### Quality assurance

Quality standards will be set to ensure that patients are treated in accordance with this protocol. All practitioners will be informed of all details pertaining to this trial. Treatments will be performed by a Korean medicine doctor having extensive clinical experience in acupuncture and pharmacopuncture. Specifically, they will be graduates of a 6-year full-time course in Korean medicine taught as a college program. They must be certified by the Korean Ministry of Health and Welfare as a Korean medicine doctor and have more than 1 year of postgraduate clinical training in a Korean medicine hospital.

The contract research organization retains responsibility for quality control, and shall meet regularly throughout the study period. The contract research organization will frequently monitor all source documents and case report forms to ensure the quality and reliability of the clinical test results. Monitoring will be conducted in accordance with the clinical test management standards and relevant regulations. The study will be executed in accordance with the Helsinki declaration and good clinical practice requirement.

### Ethics

This study protocol has been approved by the Korean Ministry of Food and Drug Safety (approval 31743). Additionally, the trial has been authorized by the institutional review boards of Ilsan Korean Medicine Hospital of Dongguk University (approval DUIOH 2018–07–003-002), Dunsan Korean Medicine Hospital of Daejeon University (approval DJDSKH-18-DR-15), and Gwangju Korean Medicine Hospital of Wonkwang University (approval 2018/14). All participants must provide informed consent before enrollment. This trial is registered with the Korean Clinical Trial Registry (CRIS), Republic of Korea.

## Discussion

Due to the limited number of high-quality randomized controlled trials, there is no reliable evidence for the safety and efficacy of pharmacopuncture [37]. Thus, this is a randomized placebo-controlled single-blind multi-center parallel clinical study, designed to evaluate the efficacy and safety of hominis placenta pharmacopuncture in the treatment of perimenopausal or postmenopausal women experiencing hot flashes.

Based on the theory of Korean medicine, pharmacopuncture is a therapeutic method to cure diseases by injecting a pharmacopuncture solution at relevant acupoints or pain points. It is a new form of acupuncture treatment combining acupuncture and herbal medicine. In acupuncture, there is physical stimulation of associated meridians and acupoints, and pharmacopuncture adds chemical stimulation to acupuncture. Since herbal extracts can be absorbed directly without passing through the gastrointestinal tract, the effects of pharmacopuncture are expected to be realized more quickly than oral herbal medicine [38].

Hot flashes are the most common symptoms related to the menopausal transition, and the primary reason that women seek medical treatment for menopausal symptoms [36]. Hot flashes are the second most worrisome menopausal symptom after weight gain [39]. Hot flashes are associated with a decreased quality of life and sleep disorders, and may play a role in influencing both the intensity and prevalence of other symptoms experienced during the menopause [40, 41].

In a systematic review of pharmacopuncture in Korea, most published papers were on hominis placenta pharmacopuncture [37]. This extract is reported to be efficacious for leg spasticity [42], dyspepsia [43], Bell’s palsy [44], osteoarthritis [45], dysmenorrhea [24, 25], and postpartum symptoms [27]. Hominis placenta is widely taken by perimenopausal or postmenopausal women as an oral medication or via pharmacopuncture in Korean medicine. However, there have been no studies on its use for the climacteric syndrome.

Western medicine has associated climacteric symptoms with the reduced function of the hypothalamic-pituitary-gonadal axis. Conversely, traditional Korean medicine frequently attributes renal deficiency as the underlying mechanism for climacteric symptoms. The normal functions of the kidneys in Korean medicine include thermoregulation, sexuality, and water homeostasis. During the menopausal transition, kidney function may decline with increasing age. In Korean medicine, many menopausal symptoms, such as hot flashes, dry mucosa, sleep disorders, and recurrent urinary tract infections, are regarded as symptoms of a deficiency of yin in the kidneys. Yin is identified with receiving and regenerative elements. The hominis placenta is known to have the power to replenish the yin in the kidneys [46].

Despite the wide use of pharmacopuncture in Korean medicine, there are several issues with treatment. First, the efficacy of hominis placenta pharmacopuncture for the treatment of climacteric syndrome needs to be evaluated in large well-designed clinical trials. However, objectification and standardization of the medication is the first step in addressing the numerous problems inherent in operating a clinical trial on hominis placenta pharmacopuncture. We standardized the medication by using PLC manufactured following the guidelines for the Unicenta injection, after obtaining approval from the Korean Ministry of Food and Drug Administration. Unicenta is a commercially available injection. Published results of clinical trials in Korea indicate that it can alleviate menopausal symptoms [47]. In Korea, hominis placenta is injected subcutaneously. It has been shown to improve menopausal symptoms and liver function.

The second problem involves blinding. In this study, the control group is administered NS, which differs in color and viscosity from PLC. Hence, medical doctors can easily identify the medication. Since this study is designed as a single-blind study, blinding of participants will be maintained by covering the syringe with opaque tape.

The third hurdle is that, due to the absence of previous studies, the power calculation was based on data from studies where hominis placenta was applied as an oral medication and from studies of acupuncture. The size of the control group was calculated based on the acupuncture studies, but we believe the NS injection in this study will be more effective than pure acupuncture due to the additional physical stimulation of the acupoints. This needs to be considered when analyzing the outcomes.

Lastly, there are various ways to evaluate hot flashes. We selected the hot flash score as the primary outcome evaluation, since it assesses both the frequency and intensity of hot flashes, enabling us to evaluate the efficacy of treatment more accurately.

This clinical trial is the first to use an objective basis to measure the efficacy and safety of hominis placenta pharmacopuncture. It is supported by national funding. We expect that this study will provide evidence for the efficacy and safety of hominis placenta pharmacopuncture. Based on the results, we plan to recommend a standard protocol for pharmacopuncture treatment and aim to substantiate clinical practice guidelines as a development of Korean medicine. We also expect hominis placenta pharmacopuncture to be used globally as an alternative therapy for hot flashes experienced by premenopausal and postmenopausal women.

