### Outcome measures

#### Primary outcome: hot flash score

The primary outcome will be the mean change in the hot flash score from baseline to 8 weeks. The hot flash score for each day will be calculated as the number of hot flashes multiplied by the average severity of the hot flashes on that day. Participants will record the number of hot flashes in a daily diary during the trial. Flashes will be scored by severity on a scale from 0 to 4 (normal 0, mild 1, moderate 2, severe 3, and very severe 4) [33]. Since the hot flash score does not have a highest value, the residual hot flash score will be used for all statistical analyses. The hot flash score measured at the baseline will be normalized to 100, and the residual hot flash score will be calculated as a percentage of the baseline score.

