### Sample size

All analyses will be undertaken by a professional statistician. Because no prior research using hominis placenta pharmacopuncture to treat hot flashes has been published, we will reference studies that have used acupuncture alone [34] or human placenta extract alone [35, 36] to alleviate hot flashes. The standard deviation was conservatively assumed based on this previous research [34–36]. The population mean of the control group was estimated using the change from the baseline in studies of acupuncture, and the population mean of the treatment group was estimated by assuming that pharmacopuncture will be more effective than acupuncture alone. Hence, the effect value was calculated by combining estimates from studies of pure acupuncture with the weighted average from studies of herbal medications.

A minimum of 68 women in the treatment group and 34 women in the control group will be necessary to identify a 20% difference with a power of 80% and α = 0.05. Assuming a total withdrawal and dropout rate of 20%, we estimate that a total sample size of 128 subjects (85 in the treatment group and 43 in the control group) is required.

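### The 80% power was derived against an acupuncture-level control, but the protocol expects saline injection to do better, so 80% is not supported for PLC versus saline

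*Protocol article*

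**What the plan says.** Protocol article, Sample size: "The population mean of the control group was estimated using the change from the baseline in studies of acupuncture". The treatment mean was set on the assumption that pharmacopuncture beats acupuncture alone, and the effect was formed by combining acupuncture estimates with a weighted average from herbal-medication studies. On the SD it says only this: "The standard deviation was conservatively assumed based on this previous research". The resulting requirement is: "A minimum of 68 women in the treatment group and 34 women in the control group will be necessary", in order to "identify a 20% difference with a power of 80% and α = 0.05". Allowing for 20% dropout, this becomes 85 and 43, or 128 in total.

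Primary outcome: hot flash score defines the analysed scale: "the residual hot flash score will be calculated as a percentage of the baseline score".

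Interventions gives the control group saline at the same points and with the same technique as PLC.

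The Discussion, on its third difficulty, notes that the control group was sized on acupuncture studies and then says "we believe the NS injection in this study will be more effective than pure acupuncture", because of extra physical stimulation of the acupoints. Its only response is: "This needs to be considered when analyzing the outcomes".

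**The concern.** The planned difference is pharmacopuncture against acupuncture. The tested difference is PLC injection against saline injection. The protocol itself expects the second comparator to be stronger than the first, yet it keeps the sample size and the stated power. It also does not say that the planned PLC mean already contains, or should be raised by, the gain it attributes to injection.

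The Discussion defers the matter to the analysis. Power is settled by the sample size, the variability and the true difference, so no analysis step can recover it afterwards.

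Readers will take 80% as the trial's chance of detecting a benefit over saline. If that chance is lower, a non-significant result could be read as PLC doing nothing when the trial was not well placed to show otherwise. The authors intend to use the results to recommend a standard protocol and support practice guidelines, so such a misreading would have consequences.

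**Working it through.** **Inputs from the protocol article.** Evaluable women: 68 and 34. Enrolled: 85 and 43. Difference 20%, power 80%, α = 0.05 (Sample size). Scale: residual score with baseline set to 100 (Primary outcome).

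**Assumptions, because the article does not give these.** The test is two-sided. The 20% means 20 points of residual score. The SD is back-solved. The size of the extra saline effect is unknown and is varied.

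**Step 1: the plan's own figures.** The dropout step reproduces: 68/0.8 = 85; 34/0.8 = 42.5, rounded up to 43; 85 + 43 = 128. The 68/34 cannot be reproduced independently without an SD, so I solve for the SD that makes it consistent:

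- √(1/68 + 1/34) = 0.2100
- standardised effect = (1.960 + 0.842) × 0.2100 = 0.588
- SD = 20/0.588 ≈ 34.0 (33.7 with the noncentral t)

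**Step 2: power for a smaller contrast.** Let saline do better than acupuncture by x points while the planned PLC mean stays where it is. The contrast is then 20 − x, and power ≈ Φ((20 − x)/SE − 1.960), where SE = SD × √(1/n₁ + 1/n₂).

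- At 68/34: SE = 34.0 × 0.2100 = 7.14
- At 85/43: SE = 34.0 × 0.1871 = 6.36

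| x | Contrast | Power, 68/34 | Power, 85/43 |
|---|---|---|---|
| 0 | 20 | 80% | 88% |
| 2 | 18 | 71% | 81% |
| 5 | 15 | 56% | 66% |
| 10 | 10 | 29% | 35% |

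For example, at 15 points and 68/34: 15/7.14 − 1.960 = 0.14, and Φ(0.14) = 0.56. The normal approximation and the noncentral t agree to within about 0.2 percentage points at every contrast below 20; the 66% is 65.5% by the first and 65.7% by the second.

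**Step 3: break-even with everyone analysed.** (1.960 + 0.842) × 6.36 = 17.8 points. If all 128 women are in the analysis, power stays at or above 80% until the contrast falls below about 17.8.

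**Step 4: the alternative in which both arms gain.** If injection adds the same x to PLC and to saline, the contrast is (20 + x) − x = 20 and power stays at 80%.

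**Step 5: sidedness.** The article does not state it. With a one-sided 0.05 test the back-solved SD is about 38, and power at 68/34 for 18, 15 and 10 points is about 72%, 59% and 34%. The pattern is the same.

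**The case against.** A reader might infer that power is simply below 80%. The document does not establish that. Both arms receive the same injection technique, and the Discussion describes pharmacopuncture as acupuncture with chemical stimulation added. The effect was built from acupuncture and herbal-medication studies, and the Discussion says the placenta data were oral, so neither source contains an injection effect. On that reading the gain from injecting could raise both arms and leave 20 points intact. This stands, and it is why the conclusion has to be conditional. It does not rescue the claim of 80%, because the protocol never says that the PLC mean gains equally. The Discussion adjusts only its view of the control and presents this as a problem for the power calculation.

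The size of any shortfall is also unknown. The SD, the arm means and the extra saline effect are not given, and a condensed article may leave the first two to the full protocol. Their absence is not the point here, and the power figures are illustrations. The full analysis set needs only one session and one evaluation, and last observation carried forward applies to all efficacy assessments. More than 102 women may therefore be analysed, and a 2-point loss would still leave about 81%.

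A reader might also see a contradiction between the claimed lack of earlier studies and the Discussion's remark on the commercial injection: "Published results of clinical trials in Korea indicate that it can alleviate menopausal symptoms". The documents do not support that inference. They do not show whether those trials report a hot flash score or a usable comparator, and the lack that the Sample size section claims concerns pharmacopuncture for hot flashes.

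Finally, the authors disclose the issue themselves. That is to their credit, but the disclosure leaves the stated power unchanged and points to a remedy that cannot work.

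**Conclusion.** The point holds in conditional form. The stated 80% belongs to pharmacopuncture against an acupuncture-level control. For PLC against saline injection it is unsupported: it is right if the injection gain is equal in both arms, and too high at 102 evaluable women if the planned PLC mean is held and saline exceeds the acupuncture response.

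In the second case, an erosion of 2 to 10 points takes power at 68/34 from 80% to between about 71% and 29%. With all 128 analysed, the range is about 81% to 35%. These figures rest on a two-sided 0.05 test, on 20% meaning points of residual score, on an SD of about 34 inferred from the sample size, and on erosion values chosen for illustration. The documents do not show which case applies or how large the erosion would be.

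**What to change.** Keep the sample size and change the text.

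1. In Sample size, state that the 80% is conditional on a 20-point difference in residual score between PLC and saline injection, if points are what is meant.
2. Say whether the planned PLC mean includes the gain attributed to the physical stimulation of injection.
3. Report power at 102 evaluable women for smaller contrasts, for example 15 and 10 points, using the SD actually assumed in planning.
4. In the Discussion, replace the sentence that defers the matter to the analysis. Say that analysis cannot restore power, and that a non-significant result will be interpreted from the 95% confidence interval for the PLC–saline difference and not as absence of effect.

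The cost is wording and a short recalculation, with no extra women. The downside is that the stated power will look less favourable.

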### Trial status

Recruitment began on 31 October 2018. The current version of the protocol is 1.9, published on 1 November 2018. Recruitment is expected to be completed by the end of December 2019. The populated SPIRIT checklist is provided as Additional file 1.

## Data Availability

The datasets used or analyzed during the current study will be available from the corresponding author on reasonable request.

## Abbreviations

MRS: Menopause Rating Scale
NS: Normal saline
PLC: Hominis placenta extract
